### Interventions and analgesia

#### Basic physical therapy

Both groups will begin basic physiotherapy (exercise) 24 h after TKA. This will include hip flexion (straight leg elevation), knee flexion extension, painless knee loosening, and ankle pumping exercises. The treatment period will be supervised by a physiotherapist, and the program will last for 30 min per day for 2 weeks. In addition, participants must perform breathing exercises with lower limb elevation within 24–48 h after TKA.

#### Scheme of standard analgesic use

Within 48 h after TKA, participants will use a patient-controlled analgesia pump. Fentanyl (Yichang Renfu Pharmaceutical Co., Ltd., Yichang, China) will be used as an analgesic drug at a continuous infusion rate of 0.25 μg/kg/h, a bolus dose of 0.15 μg/kg, and a 10-min lockout time. In addition, all participants will begin oral administration of celecoxib capsules (Pfizer Pharmaceutical Co., Ltd., New York, USA), at a dosage of 200 mg once daily, 72 h after operation.

#### Opposing EA

According to the new standard of “International Acupuncture Nomenclature” [39], the acupoints of *Yinlingquan* (Spleen 9, SP9), *Yanglingquan* (Gallbladder 34, GB34), *Futu* (Stomach 32, ST32), and *Zusanli* (Stomach, ST36) will be applied to the healthy lower limb (contralateral side) (Fig. 5). After skin disinfection, a sterile rubber pad (8 × 10 mm, Suzhou Medical Supplies Factory, China) will be placed on the above acupoints, and the acupuncture needle (0.25 × 40 mm, Suzhou Medical Supplies Factory, China) will pierce the skin at a depth of approximately 3 cm. The acupuncturist will use the same acupuncture technique to produce feelings of *de qi* (patient sensations of acidity, sinking, distension, and fever at the acupoints). After achieving *de qi* sensation, the Huatuo SDZ-II EA apparatus (Suzhou Medical Supplies Factory, Suzhou, China) will be used to continuously stimulate the acupoints. The frequency of the instrument will be adjusted to 40 Hz, and the pulse width will be adjusted to a constant current square wave of 1 ms. It is appropriate to gradually increase the pulse intensity until it becomes unbearable. The opposing EA group will undergo a 3-day treatment course consisting of 30-min sessions once daily.

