**Methods:**

This is a randomized sham-controlled single-blind clinical trial. Patients will be allocated randomly to two parallel groups (A: opposing electroacupuncture group; B: sham opposing electroacupuncture group). The Yinlingquan (SP9), Yanglingquan (GB34), Futu (ST32), and Zusanli (ST36) acupoints will be used as the opposing needling sites in both groups. In group A, the healthy lower limbs will receive electroacupuncture, while in group B, the healthy lower limbs will receive sham electroacupuncture. At 72 h after unilateral TKA, patients in both groups will begin treatment once per day for 3 days. Functional magnetic resonance imaging will be performed on all patients before the intervention, after unilateral TKA, and at the end of the intervention to detect changes in brain activity. Changes in pressure pain thresholds will be used as the main outcome for the improvement of knee joint pain. Secondary outcome indicators will include the visual analogue scale (including pain during rest and activity) and a 4-m walking test. Surface electromyography, additional analgesia use, the self-rating anxiety scale, and the self-rating depression scale will be used as additional outcome indices.

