### Exit criteria and management

Exit criteria include (1) participants request the suspension of the trial process, (2) severe postoperative complications (e.g., pulmonary embolism, infection), and (3) intra-treatment side effects. Participants who drop up during the trial will be treated with routine analgesia.

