### Patient safety

The study will be conducted in accordance with the guidelines and principles of the Declaration of Helsinki. Adverse events caused by acupuncture, such as subcutaneous hemorrhage, dizziness, or other severe events, will be dealt with immediately and recorded in detail in the case report form. Each patient will be compensated to participate in the study.

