### Adverse events of EA

The main EA-related complications include dizziness, acupuncture stagnation, acupoint hematoma, pain > 2 h after continuous acupuncture, and bleeding. Any such adverse events during the trial will be recorded.

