FMRI is a large-scale neural network technique. As the main type of fMRI, blood oxygen level-dependent fMRI measures neuronal activity using the ratio of oxyhemoglobin to deoxyhemoglobin as a contrast mechanism [61]. With the advantages of high imaging speed, non-radiation, and non-invasiveness [62, 63], it has become a commonly used neuroimaging technique in the research of the central mechanism of acupuncture [64, 65]. Relative to task-related fMRI, rs-fMRI has the advantage of providing more comprehensive information on the functional architecture of the brain [61]. Using rs-fMRI, some investigators have found that acupuncture can exert an analgesic effect by directly regulating the anterior cingulate gyrus. Their results also suggested that acupuncture on the opposite side and ipsilateral side can induce different brain mechanistic changes [33].

In this trial, we will adopt direct quality control measures to reduce bias and improve the reliability of the results. In addition to establishing strict inclusion and exclusion criteria at the stage of participant recruitment, demographic characteristics such as age and handedness will also be applied as inclusion criteria. The mode of operation and the type and dose of perioperative medication will be regulated as much as possible, and factors that may affect brain activity, including coffee drinking or alcohol and drug abuse, will also be considered. The acupuncturist will receive standardized training before the trial and carry out all treatments in accordance with standard operating procedures. During acupuncture, unnecessary communication between the acupuncturist and the patient will be prohibited. The personnel responsible for the analysis will be trained and blinded to the test group.

In summary, the purpose of this trial is to study the main mechanism of opposing EA in the management of acute pain after TKA by analyzing the correlation between changes in brain activity and clinical variables. We hope that our findings can provide a visual reference for the clinical application of opposing needling after TKA.

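### The only intensity rule for active electroacupuncture sets its endpoint at an unbearable stimulus; maximum tolerable intensity was probably meant, but the sentence is wrong as written

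*Protocol article*

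**What the plan says.** The Opposing EA section of the protocol article fixes the active treatment in some detail: four acupoints on the healthy leg, 40 Hz, a 1 ms constant-current square wave, and the course length. On intensity it says only: "It is appropriate to gradually increase the pulse intensity until it becomes unbearable". On the course it says: "The opposing EA group will undergo a 3-day treatment course consisting of 30-min sessions once daily". The abstract gives the start: "At 72 h after unilateral TKA, patients in both groups will begin treatment once per day for 3 days".

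Four other places bear on tolerability:

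- Exit criteria and management lists "intra-treatment side effects" as a reason to leave the trial.
- Patient safety says that adverse events caused by acupuncture "will be dealt with immediately and recorded in detail in the case report form".
- Adverse events of EA lists the complications to be recorded, among them "pain > 2 h after continuous acupuncture, and bleeding".
- The Discussion says that the acupuncturist will "carry out all treatments in accordance with standard operating procedures". Those procedures are not shown.

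**The concern.** Intensity is part of the dose. The usual titration endpoint is the strongest stimulus the patient can tolerate; this sentence names the point at which tolerance has been exceeded. The patients have acute postoperative pain, the treatment is meant to relieve it, and the current goes through their healthy leg.

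Two things are at stake. One is safety and comfort: an acupuncturist who follows the text would take a patient to an intolerable stimulus. The other is reporting: the article states that it follows STRICTA, so a reader repeating the treatment would take this as the intensity rule.

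The objection is to the word that is printed. A condensed article may leave out a milliampere cap or an intensity log, and their absence is not part of this point.

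**Working it through.** There is no figure to reproduce and no calculation to run. The check is whether anything in the document corrects or overrides the sentence.

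1. **Could another stated setting bound the intensity?** Opposing EA gives frequency (40 Hz), pulse width (1 ms) and waveform (constant-current square wave). None of these is an amplitude, so none limits intensity.

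2. **Does another section give a different rule?**

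| Section | What it provides | Sets a tolerable limit? |
|---|---|---|
| Background | General remark that electroacupuncture uses various current levels | No |
| Sham opposing EA | Device connected with no electrical output; trained, experienced acupuncturists in both groups | No |
| Study design and participants | Freedom to withdraw at any time | No |
| Exit criteria and management | Exit for side effects during treatment | No; acts after the event |
| Patient safety | Adverse events handled at once and recorded | No; acts after the event |
| Data management and monitoring | Weekly ethics committee supervision; safety monitored at team meetings | No |
| Adverse events of EA | List of complications to record | No; acts after the event |
| Discussion | Treatment according to standard operating procedures | Unknown; not shown |

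One intensity endpoint is stated, and nothing visible replaces it.

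3. **Does the reading of the sentence matter?** As a stop point, titration ends when the stimulus has become unbearable, so the limit is passed at least briefly. As a level to reach and keep, the stimulus stays there. The text does not say which is meant and gives no step-down, so it does not establish that the level is held for the session. On both readings the named endpoint is beyond tolerance; what differs is how long the patient spends there.

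4. **How often could the rule apply?** One session per day × 3 days = 3 sessions per active patient, each of 30 minutes. This assumes that intensity is set afresh at each session, which the article does not state. The count is of occasions and does not measure harm.

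**The case against.** The strongest reply is that this is a language slip and not a design decision. The article has others: a misprint for dropping out in the exit criteria, an instruction in the timed walking test that appears to confuse soon with fast, and an unidiomatic name for a chi-squared test. Gradual increase up to a limit fits the ordinary practice of stopping at tolerance, and nothing suggests that intolerable stimulation was intended. Trained acupuncturists, freedom to withdraw, weekly ethics supervision and standard operating procedures all make literal execution unlikely. Nothing in the sample size, analysis or inference depends on the sentence, so on this view it is a minor erratum.

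Much of that stands. A slip is the likeliest explanation, literal compliance is unlikely, and there is no consequence for inference. It is also right that the session count carries little weight and that a sustained 30 minutes at an unbearable level cannot be read into the text.

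The conclusion still stands. The sentence is a positive dosing instruction in the section that defines the intervention, so the allowance for what a condensed article leaves out does not cover it. The safeguards lower the chance that it is followed; none changes what it says. If the operating procedures have it right, the article misreports them and still needs correcting.

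**Conclusion.** The point holds: the intensity endpoint for active electroacupuncture is wrong as written and should be corrected. Confidence is high for that narrow statement, which rests on the text alone.

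It is not high for any actual harm. That would depend on acupuncturists following a word that was probably not meant, and on what the unseen operating procedures say. Its size cannot be estimated, since the document gives no current value and no rate of intolerance. The countable facts are one stated endpoint, no visible correction of it, and up to three sessions per active patient at which it could apply. The trial's conclusions are not affected.

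**What to change.** Replace the sentence with: *Gradually increase the pulse intensity to the maximum level the patient can tolerate, and reduce it at once if it becomes unbearable.* Confirm that the standard operating procedures say the same, and notify the two acupuncturists named by role under Study design and participants. The Trial status section describes recruitment as under way, so at the time of the document a correction could still reach treatment sessions.

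The cost is one corrected sentence, one check of the procedures and one notice. It needs no new data field and no change to the sample size or analysis. If maximum tolerable intensity was intended, the dose is unchanged. If it was not, the rule itself has to change for the patients' sake.

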**Fig. 5 Fig5:**
[figure not shown]
Location of acupoints for the opposing electroacupuncture and sham opposing electroacupuncture groups

#### Sham opposing EA

In the sham opposing EA group, a pragmatic placebo needle will be used [28]. As in the opposing EA group, the *Yinlingquan* (Spleen 9, SP9), *Yanglingquan* (Gallbladder 34, GB34), *Futu* (Stomach 32, ST32), and *Zusanli* (Stomach, ST36) acupoints will be selected. The blunt needle (size 0.25 × 30 mm, Hwato Brand, Suzhou Medical Appliance Factory, China) used at these acupoints will not penetrate the skin but will affix to the surface of the skin through an adhesive pad (Fig. 5). The same acupuncture manipulation as that of the opposing EA group will be used to simulate the genuine acupuncture process. A Huatuo SDZ-II EA apparatus (Suzhou Medical Supplies Factory, Suzhou, China) will be connected to these acupoints through special electrode wires without electric output. The sham needle will remain in the adhesive pad for 30 min during each treatment session. The process of sham opposing EA is similar to that of opposing EA, but the former does not involve skin penetration, needle manipulation, or electrical output. The sham opposing EA group will also undergo a 3-day treatment course consisting of 30-min sessions once daily. Both groups will be treated by experienced acupuncturists with standardized training.

To ensure treatment compliance, participants will be required to register for treatment. Throughout the trial, the participants will be treated separately to prevent communication between participants. Routine care pathways (including the use of any drugs) will be carried out as standard and will not be affected by the implementation of EA or sham EA. Participants who completed the trial will receive free elastic band and rehabilitation ball to assist in the rehabilitation of lower limb muscles. In addition, we will give them a 6-month follow-up and postoperative rehabilitation exercise guidance.

### MRI data acquisition

The functional MRI (fMRI) data will be acquired by a clinical 1.5-T whole-body MRI scanner (United Imaging, Shanghai, China) at the MRI Center in Guanghua Hospital, Shanghai University of Traditional Chinese Medicine. The participants will be asked to wear soundproof earplugs during the scan, and the examiner at the MRI center will add a sponge between the patient’s head and the head coil to reduce noise and to discourage patient head movement. The participants will be instructed to stay awake and relaxed and to close their eyes during the scan and not think of anything in particular. Each patient will undergo two MRI scans; the first scan will be performed before the first intervention after surgery, and the second after all interventions are completed. After each scan, participants will complete a simple questionnaire to determine if they fell asleep during the scan.

Resting-state fMRI (rs-fMRI) images will be generated using a rapid-gradient echo-planar imaging sequence with the following settings: repetition time, 3,000 ms; echo time, 30 ms; flip angle, 90°; field of view, 225 × 225 mm^2^; acquisition matrix, 64 × 64; 43 slices; slice thickness 3.5 mm; voxel size, 3.52 × 3.52 × 3.52 mm^3^; and bandwidth, 2250 Hz/pixel. Each scan will require 12 min 13 s. Three-dimensional T1-weighted magnetization-prepared rapid-gradient echo sagittal images will be captured using the following parameters: repetition time, 10.4 ms; echo time, 4.4 ms; inversion time, 750 ms; flip angle, 10°; matrix, 256 × 232; slice thickness, 1 mm; and voxel size, 1 × 1 × 1 mm^3^. Each scan will require 3 min 32 s.

### Outcome evaluations

The clinical evaluations will measure knee pain and physical function. The primary outcome measure will consist of the pressure pain thresholds (PPTs), and the secondary outcome indicators will include the visual analogue scale (VAS), including pain during rest and activity, and the 4-m walking test (4MWT). Additional outcome indicators will comprise surface electromyography (sEMG), the self-rating anxiety scale (SAS), the self-rating depression scale (SDS), and the use of additional analgesics. Data regarding PPTs, VAS, and the 4MWT will be collected at baseline, 30 min before each acupuncture treatment, and immediately after each acupuncture treatment. sEMG, SAS, and SDS data will be collected at baseline, before the first acupuncture session after the operation, and after all interventions have been completed. The use of additional analgesics will be assessed at the end of the intervention period.

#### Primary outcome

PPTs are quantitative sensory tests that are widely used in the prediction and evaluation of clinical therapeutic effects in patients with KOA [40–43]. An experienced trained clinician ([name]) will perform all PPT measurements using the FDX-50 portable pain tester (Wagner Instruments, Greenwich, CT, USA) to minimize measurement variability. The specific operation is as follows: the patient will lie down in the supine position, and two points of the operated knee joint will be used for testing: (1) lateral point: located 3 cm lateral to the midpoint of the lateral edge of the patella, and (2) medial point: located 3 cm medial to the midpoint of the medial edge of the patella. A 1-cm^2^ probe will be applied perpendicular to the skin, and the pressure will be maintained at 10 kPa/s. Patients will be instructed to say “stop” the first time they feel pain, at which point the PPT readings will be recorded. Three readings will be taken at each site, with the final two readings averaged to increase the reliability. There will be a small change in the probe position of the pain meter on the skin between each reading to avoid sensitization of the test area [44].

#### Secondary outcomes

The VAS score will be used to measure pain. Postoperative pain assessment should evaluate pain at rest and with movement [45]. Independent evaluators who do not participate in acupuncture will perform the VAS assessments (participants will be asked to indicate the intensity of pain at the most painful point while resting and walking). In this experiment, a line segment of 10 cm will be used as a scale, and the ends will be marked as 0 (painless) and 100 (severe). Patients will draw a vertical mark and horizontal line crossing to evaluate their own pain and the distance from 0 to the marked point will be measured to determine the VAS score; the higher the score, the higher the degree of pain [46]. Throughout the trial, in addition to evaluating resting pain at 6 h after the operation, pain will be evaluated before and after each intervention after the operation.

The 4MWT can be used as a supplementary index to evaluate lower limb function after orthopedic surgery, and the test-retest reliability is good [47]. We will use a 50-m corridor in the orthopedic ward for evaluation because this test requires additional distances to accelerate and decelerate. We will mark the 8-m path needed for the 4MWT in the corridor; the first 2 m of this path will be marked with an acceleration warning, and the final 2 m will be marked with a deceleration warning. These extra spaces for acceleration and deceleration will not be used as data collection areas. The starting and end points of the 4-m path will be marked with colored inelastic tape. When the patient’s leg crosses the acceleration starting point, the clock starts. Once the patient’s leg passes the 4 m mark, the stopwatch stops, signaling the patient to slow down and stop. Before the test, we will provide verbal guidance to the patients, explain the detailed test procedures, and tell patients to walk as soon as possible. All patients will use walkers as aids to ensure safety [47].

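### The 4-m walking test, a secondary outcome, has a contradictory timing rule: the clock starts in a zone that the same paragraph excludes from measurement, and the stop mark has no stated origin

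*Protocol article*

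**What the plan says.** The test is described in the Protocol article under Secondary outcomes, and Outcome evaluations lists it as secondary beside the VAS.

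- Layout: "We will mark the 8-m path needed for the 4MWT in the corridor". The first 2 m are for acceleration and the last 2 m for deceleration.
- Status of the end zones: "These extra spaces for acceleration and deceleration will not be used as data collection areas".
- Marking: "The starting and end points of the 4-m path will be marked with colored inelastic tape".
- Clock start: "When the patient’s leg crosses the acceleration starting point, the clock starts".
- Clock stop: "Once the patient’s leg passes the 4 m mark, the stopwatch stops, signaling the patient to slow down and stop".

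The test is done at baseline and before and after each of the three daily treatments (Outcome evaluations; Opposing EA).

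**The concern.** The layout and the exclusion sentence point to one timed segment, between the two tapes. The clock-start sentence points to another, beginning at the line where the patient sets off. Both cannot be followed. The stop rule adds to the doubt, because it does not say from where the 4 m is counted.

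An evaluator who works from the tapes and one who works from the clock sentence would record different times for the same walk. Study design and participants names two outcome evaluators. The schedule gives 1 + 3 × 2 = 7 tests per patient, or up to 7 × 80 = 560 in the trial. A change of segment between two of these tests would look like a change in walking ability.

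**Working it through.** **Inputs from the Protocol article (Secondary outcomes).** Path 8 m; acceleration zone 2 m; deceleration zone 2 m; tapes at both ends of the 4-m path; clock starts at the acceleration starting point; clock stops at the 4 m mark.

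**Step 1: reproduce the layout.** 2 + 4 + 2 = 8 m, as stated. With the end zones excluded, the timed segment runs from 2 m to 6 m, which is where the two tapes lie.

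**Step 2: apply the clock rule literally.** The acceleration starting point is 0 m. The stop has two readings.

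- The 4 m mark is the end tape: 0–6 m is timed, so 2 + 4 = 6 m.
- The 4 m mark lies 4 m from the acceleration line: 0–4 m is timed, and 2/4 = half of it is the acceleration zone.

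The first reading fits better. Passing the mark is the patient's cue to slow down, which suits the end tape, where the deceleration zone begins. Under the second, the patient would be slowing halfway along the taped path. Neither reading gives 2–6 m.

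**Step 3: size at constant speed.** The time over 0–6 m relative to 2–6 m is 6/4 = 1.5.

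**Step 4: size from a standing start (illustrative).** Assume constant acceleration *a* from rest up to a steady speed *v*, reached within the first 2 m. The time to distance *x* is then x/v + v/(2a), and the time over 2–6 m is 4/v. The ratios to the intended time are:

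- 0–4 m: 1 + v²/(8a)
- 0–6 m: 1.5 + v²/(8a)

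The documents give neither *v* nor *a*. The assumed ranges are 0.3 to 1.0 m/s and 0.3 to 1.0 m/s².

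| v (m/s) | a (m/s²) | 2–6 m | 0–4 m | 0–6 m |
|---|---|---|---|---|
| 0.3 | 1.0 | 13.33 s | 13.48 s (+1.1%) | 20.15 s (+51.1%) |
| 0.6 | 0.5 | 6.67 s | 7.27 s (+9.0%) | 10.60 s (+59.0%) |
| 1.0 | 0.3 | 4.00 s | 5.67 s (+41.7%) | 7.67 s (+91.7%) |

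The first and last rows are the extremes of the assumed ranges. At 0.3 to 0.6 m/s, the 0–4 m excess is about 1% to 15%.

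**Step 5: effect on the group comparison.** If everyone is timed over 0–6 m at constant speed, every time is multiplied by 1.5. The mean difference and its SD are both multiplied by 1.5, so the *t* statistic is unchanged, and so are the Mann-Whitney ranks. A standing start adds the term v/(2a), which is start-up time and a source of noise. If the segment varies, the picture changes: in the middle row, moving from the tapes to the 0–6 m rule adds 10.60 − 6.67 = 3.93 s with no change in the patient.

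**The case against.** The strongest reply is that this is a wording slip. The rest of the paragraph describes a coherent test, and taping the start of the 4-m path has little purpose unless timing begins there. Nothing shows that evaluators follow the odd sentence. That stands as far as practice is concerned. It does not clear the text, because the odd sentence is the operative instruction.

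A reader might go further and infer that the outcome is wrong for every patient at every visit, or that the group difference is distorted. The document supports neither. It does not show which line is used. Allocation is randomised 1:1 and evaluators are blinded (Randomization and blinding), so a rule applied uniformly falls on both arms alike.

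A reader might also infer that gait speed is understated by a third (1 − 4/6). That requires speed to be computed as 4 m divided by a 6-m time, and the article describes only a stopwatch time. Whether results would be comparable with 4-m walking tests elsewhere cannot be judged from this document either.

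**Conclusion.** The concern holds as an internal contradiction in the operational definition of a secondary outcome. On the literal wording, the timed course is 0–6 m or 0–4 m, not the 2–6 m segment laid out. On the likelier 0–6 m reading, times are 1.5 times the intended ones at constant speed. With a standing start they are about 51% to 92% longer under the assumed speeds and accelerations. On the 0–4 m reading the excess is about 1% to 42%. The standing-start figures are illustrative.

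The real risk is inconsistent application across evaluators, patients or visits, which is possible but not shown. Severity is moderate. Pressure pain threshold, the primary outcome, is measured separately and is unaffected, and so is the sample size.

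**What to change.** Replace the start and stop sentences with one rule: the clock starts when the leg crosses the start tape of the 4-m path and stops when it crosses the end tape. This also removes the undefined 4 m mark.

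Trial status reports that recruitment is under way, so ask the evaluators which lines they have used so far and record the answer. If they used the tapes, nothing else changes and no data need to be set apart. Only if another segment was timed, flag those values and handle them separately or in a sensitivity analysis. A blanket rule against pooling, made before practice is known, could split valid repeated measurements for no reason.

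The cost is one sentence, a short retraining note and one query to the evaluators. The plan already provides for the tapes.
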